**Analytic plan**

Statistical analysis: Planned T-tests and chi-squared tests will be applied to assess differences between the two treatment groups. Intention to treat analysis (ITT) will be applied to examine differences in baseline and post-treatment scores. All outcomes will be treated as continuous. A random-effect model will be used to estimate treatment effects including five assessment time points and counsellor ID as random effects to account for within-person correlation across time and between-correlation by counsellor. A post-hoc analysis using the baseline measurement as a covariate will be implemented. Gender, age, and other relevant sociodemographic characteristics will be examined separately as covariates. Missing data will be imputed using chain equations command in Stata which allows for pooling of data according to Rubin’s rules.

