**Study participants**

Participants will comprise male and female adults (18 years of age or older) who are members of the Chin, Kachin, and Rohingya communities. Inclusion criteria are (a) meeting criteria for at least one of the included CMDs (PTSD/CPTSD, MDD, GAD, and PCBD)[11]; (b) witnessed or experienced at least one traumatic event related to mass conflict; and (c) endorsed at least one stressor on the ASI. Exclusion criteria are than 18-years of age; intellectually disabled or cognitively impaired based on obvious indicators of disability; presence of overt psychosis (as assessed using the WHO mhGAP protocol) [14].

All participants will be assessed at baseline, immediately post-treatment, and at 12-month follow-up. Figure 1 shows the flow of participants through the trial.

Figure 1. Flow Diagram

Post Intervention

Initial assessment for eligibility

Informed consent

Baseline assessment

Randomization

N=331

CBT: 6 Weekly sessions

of 45 minutes

IAT: weekly sessions

of 45 minutes

Enrolment

Allocation

6 weeks Post-treatment

assessment

Follow-up

12 months follow-up

assessment

*Sample size*

The International Society for Traumatic Stress Studies (ISTSS) has provided guidance concerning the magnitude of outcome differences that should be regarded as clinically meaningful in comparing one active psychotherapy over another in the trauma field [15]. Based on this guide, we estimated that a minimum of 150 participants were needed in each arm to achieve a moderate effect size of 0.50 and a design effect of 1.5, based on 80% power and a two-tailed 5% significance level. This calculation assumed an attrition rate of 50% in view of the pattern of substantial resettlement to third countries that could occur based on recent precedence over the period of follow-up.

*Randomization and masking*

Eligible participants will be randomized to either the IAT or CBT arm. Participants who meet the inclusion criteria will then be randomized based on a 1:1 ratio using a computer-generated randomization sequence. An off-site research assistant will oversee the randomized assignment, a process fully concealed from the counsellors who will be informed about treatment assignments via the trial coordinator. Refugees will be blind to their diagnostic status but not their treatment condition. The statistician involved in data management, analysis and interpretation of results will be blind to the participants’ treatment condition.

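### Three analyses of the treatment comparison are named with none primary, and the baseline-adjusted one, which is planned and at least as precise as the others, is ranked lowest as post hoc

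*Protocol*

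**What the plan says.** The Analytic plan section of the protocol gives these statements on the comparison of IAT with CBT, in this order:

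- "Planned T-tests and chi-squared tests will be applied to assess differences between the two treatment groups". No outcome, time point or covariate is attached to the sentence.
- An intention-to-treat analysis is to look at differences in baseline and post-treatment scores.
- A random-effect model is to estimate treatment effects. It has five assessment time points, and counsellor ID enters as a random effect.
- "A post-hoc analysis using the baseline measurement as a covariate will be implemented". This is the only sentence that adjusts for baseline.
- On the remaining covariates: "Gender, age, and other relevant sociodemographic characteristics will be examined separately as covariates".

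All outcomes are to be treated as continuous. The section does not say which analysis is primary or how baseline enters the random-effect model. Under Study participants, every participant is to be assessed at baseline, immediately post-treatment and at 12 months. The Sample size text there mentions neither a baseline correlation nor covariate adjustment.

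**The concern.** Two things are fixed badly in what the protocol states.

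First, an analysis written into the plan beforehand is not post hoc. The label is wrong on its face, and it lowers the standing of the analysis that makes best use of a score the trial already collects.

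Second, the treatment difference can be read from a t-test, from the random-effect model or from the baseline-adjusted analysis, with further versions as covariates are examined one at a time. With no order among them, and several primary outcomes, there is room to choose an estimate after seeing the data.

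Precision is at stake as well. An unadjusted comparison leaves any chance baseline difference between arms in the estimate. A change score removes it but over-corrects when the correlation between baseline and outcome is modest. Adjusting for baseline avoids both.

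**Working it through.** **1. Inputs.** From the Sample size text: "a minimum of 150 participants were needed in each arm", "a moderate effect size of 0.50", "a design effect of 1.5", "based on 80% power and a two-tailed 5% significance level", and "This calculation assumed an attrition rate of 50" per cent. The flow diagram gives 331 randomised. The correlation rho between baseline and outcome is my assumption, because the protocol gives none; I use 0.3, 0.5 and 0.7.

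**2. The plan's own figure.** For d = 0.50, two-sided 5% and 80% power, n = 2(1.96 + 0.84)²/0.50² = 62.8, so 63 per arm. Then 63 × 1.5 = 94.5, rounded to 95, and 95/0.5 = 190 per arm. The stated 150 is not reproduced. A one-sided 5% test gives 50 × 1.5/0.5 = 150 exactly, but the text says two-tailed. This is a separate sample-size error; here it only explains why unadjusted power starts below 80%.

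**3. Does the random-effect model use baseline?** The second footnote records an initial design with further assessments at 3, 6 and 12 months. With baseline and post-treatment that makes five, the number of time points in the model. Baseline is therefore very probably an outcome occasion in it.

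**4. Variance of the three contrasts** at one follow-up time, with SD 1 at both occasions:

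- unadjusted: 1
- change from baseline: 2(1 − rho)
- baseline-adjusted: 1 − rho²

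The change score beats the unadjusted comparison only when 2(1 − rho) < 1, that is rho > 0.5. Since 1 − rho² ≤ 1, and 1 − rho² = (1 − rho)(1 + rho) ≤ 2(1 − rho), adjustment is never less precise than either.

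**5. Effective sample size.** 150 × 0.5 = 75 completers per arm, and 75/1.5 = 50. With 331 in total: 165.5 × 0.5/1.5 = 55.2. Dividing 50 by the variances in step 4 gives:

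| rho | unadjusted | change score | adjusted |
|---|---|---|---|
| 0.3 | 50 | 35.7 | 54.9 |
| 0.5 | 50 | 50.0 | 66.7 |
| 0.7 | 50 | 83.3 | 98.0 |

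**6. Power**, two-sided 5%, noncentral t with noncentrality 0.5 × √(n/2) and 2n − 2 degrees of freedom, n being the effective size per arm:

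| rho | unadjusted | change score | adjusted | adjusted, 331 in total |
|---|---|---|---|---|
| 0.3 | 0.70 | 0.55 | 0.74 | 0.78 |
| 0.5 | 0.70 | 0.70 | 0.82 | 0.85 |
| 0.7 | 0.70 | 0.89 | 0.94 | 0.96 |

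Unadjusted power with 331 in total is 0.74. The normal approximation gives values within about one percentage point (for example 0.705 in place of 0.697 for the unadjusted case).

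**7. Correlation needed for 80%.** The t-based calculation needs an effective n of about 63.8 per arm. At 150 per arm, 1 − rho² = 50/63.8 = 0.784, so rho is about 0.46. With 331, 55.2/63.8 = 0.865, so rho is about 0.37. The normal approximation gives about 0.45 and 0.35.

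**The case against.** The strongest reply is that the protocol already names its estimator. The random-effect model is the analysis said to estimate treatment effects, and it accounts for within-person correlation and for counsellor. The t-test sentence is paired with chi-squared tests, which do not suit outcomes that are all continuous, so it may only describe the groups. Model form and covariate sets are also commonly left to the SAP, which is not shown.

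Much of this stands. A reader might infer that unadjusted t-tests are the main efficacy analysis and that the baseline score is thrown away. The text supports neither: the first is left open, and baseline very probably sits in the model. If that model holds baseline means equal across arms, little or nothing is lost against covariate adjustment. The step from 0.70 to 0.82 is therefore the gain over a single-time unadjusted test, not a measured loss for the planned model.

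Two things survive. The post-hoc label and the unranked list are stated in the protocol, so they are not details awaiting the SAP. And nothing in the text says that baseline means are constrained; without that, the model's treatment-by-time contrast is roughly the change score above.

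**Conclusion.** The point holds as a defect of ranking and labelling with an avoidable risk to precision. The baseline-adjusted analysis is at least as precise as the unadjusted comparison and the change score at every rho, yet it has the lowest standing. Against an unconstrained change-type contrast the illustrated difference in power is 0.74 versus 0.55 at rho 0.3, 0.82 versus 0.70 at 0.5, and 0.94 versus 0.89 at 0.7.

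These figures assume equal SDs at baseline and follow-up, an effect of 0.50 in unadjusted SD units, a design effect unchanged by adjustment, and attrition as lost data with no credit for the planned multiple imputation. Requiring a disorder at entry and following up to 12 months could both lower rho.

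A reader might infer that adjustment restores 80% power. That is conditional on rho, fails at 0.3 for either sample size, and does not replace correcting the sample-size calculation. Nor can one infer that randomisation is simple: the protocol gives a 1:1 computer-generated sequence and describes no stratification, which is not the same statement. Randomised inference remains valid under any of the analyses.

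**What to change.** In the Analytic plan, and in the SAP if one exists:

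- Name one primary analysis: the random-effect model with counsellor effects, post-treatment and 12-month scores as outcomes, and the baseline score as a fixed covariate. An equivalent choice is to keep baseline as an occasion with one common mean across arms. Use one or the other, not both, so that baseline is not used twice.
- Delete the post-hoc label.
- Limit t-tests and chi-squared tests to description.
- Keep models with sociodemographic covariates as sensitivity analyses.
- State the assumed rho wherever baseline adjustment is used to support power, and correct the sample-size calculation as its own item.

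The cost is a wording change. It needs no new data, visits or participants.

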**Ethics, consent and permissions**

This study was approved by the Human Research Ethics Committee (HREC) of the University of New South Wales and Institutional Review Board, Perdana University, Malaysia. All participants will be asked to provide written consent prior to baseline and follow-up assessments and their allocated treatment.

**Discussion**

Our RCT aims to assess the efficacy and feasibility of a novel intervention, Integrative Adapt Therapy (IAT), specifically designed to strengthen the resilience and capacity of refugees to cope with the undermining of the psychosocial systems that support mental health and well-being. The overarching goal of IAT is to provide refugees with a coherent framework that assists in making sense of their experiences and their emotional and interpersonal reactions to the challenges they confront within the family and community context. As such, IAT offers an alternative approach to psychotherapeutic interventions for refugees. The adoption and wider use of IAT will await the outcome of ongoing trials, including amongst multi-ethnic Myanmar refugees, examining the efficacy, cultural, and contextual adaptability of the method. A naturalistic trial is currently being conducted amongst the Rohingya refugees in Bangladesh. Planned RCTs examining the effectiveness of IAT in primary care settings in Bangladesh and Australia will be conducted at a later stage.

References

1. UNHCR: **UNHCR projected global resettlement needs**. In: *23rd Annual Tripartite Consultations on Resettlement.* Edited by UNHCR. Geneva; 2018: 1-84.

